# Table 1. Summary of proposed economic and health outcomes for cost-effectiveness analysis.

| Proposed cost outcomes to be included | | | | Health outcomes measured | | |
| --- | --- | --- | --- | --- | --- | --- |
| Policy change | Delivery of sIPTc | Cost offsets***** | Patient & community | Morbidity | Mortality | DALY |
| **** | **** | **** | **** | **** | **** | **** |

*Source (CEWG)*

***** These consist mainly of costs saved due to less treatment seeking resulting from less malaria morbidity

**** Indicates these data are to be measured prospectively for the given study.

5. Impact on health seeking behaviors

It is possible that sIPTc may affect treatment-seeking behavior for malaria, for example if it is misinterpreted as providing long-term protection similar to that of vaccines. As a result, adequate treatment could be delayed. Conversely, increased awareness of malaria as a result of sIPTc may enhance use of other preventive and curative measures. It is therefore important to know how people perceive sIPTc, and how it influences health behavior. A number of case studies will be made of episodes of childhood febrile illness to determine the influence of the intervention on treatment seeking behaviors. In order to place this in a broader context, community focus group discussions will be carried out to investigate people’s understanding of malaria, their treatment priorities, and their perceptions of the intervention. As the use of ACT may also influence people’s interpretations of both malaria and sIPTc, their treatment seeking behavior and their response to the introduction of the intervention will also be studied.

As the long-term success and sustainability of this intervention depend on the adequate functioning of a system of community participation, the interaction between health services, community representatives involved in the intervention and the target population will be studied using qualitative methods, in order to understand problems that arise and to allow the identification of potential impediments to implementation.

TIME TABLE

**Baseline survey and implementation study preparatory phase**

1st July 2006 – 31 March 2007

Intervention

1st April 2007 – 31 August 2007 preparatory phase 2

1st September 2007 – 31 November 2007 intervention year 1

1st December 2007 – 31 August 2008 preparatory phase 2

1st September 2008 – 31 November 2008 intervention year 2

1st December 2008 – 31 August 2009 preparatory phase 3

1st September 2009 – 31 November 2009 intervention year 3

Evaluation

1st April 2007 – 31 August 2007 preparatory phase

1st September 2007 – 31 August 2008 evaluation year 1

1st September 2008 – 31 August 2009 evaluation year 2

1st September 2009 – 30 June 2010 final evaluation

**PROJECT MANAGEMENT AND DISSEMINATION PLAN**

The grant holding institution will be the University of Dakar, Department of Medical Parasitology, headed by [name]. The two co-principal investigators will assist the two principal investigators.

A “Project Advisory Committee” will be created with representatives of the Senegalese Ministry of Health and Prevention, the heads of the medical regions of Fatick, Thies and Diourbel, WHO and UNICEF. This group will meet every three months.

Finally, a “Project Directorial” will be formed. It will include the investigators listed in page 2. Selected members of this group will meet on a monthly basis, or more frequently if needed.

DATA AND SAFETY MONITORING

The trial will have a Data and Safety Monitoring Board (DSMB), consisting of members with clinical, statistical and local knowledge. Their responsibilities will be as follows:

1. To insure the investigators’ compliance with the study protocol

2. To monitor the progress of the trial (i.e. data and safety concerns of the study)

3. To make recommendations on further progress of the study

The DSMB members will meet once a year in Dakar, preferably in August, just before the drug administration starts. A second meeting each year, by conference call, is also envisaged. All members of this board will be paid by the project.

A local safety monitor designated by the DSMB will regularly visit the site.

ETHICS

As decided at the Dar es Salaam meeting in February 2005, communal informed and written consent will be obtained from trusted and respected community leaders. The study will explain the need to find an efficient way for large-scale prevention of malaria in children less than five years of age, using sIPTc.

Ethical approvals of the study will be sought from both:

- The Ethics Committee of the Senegalese Government

- The Ethics committee of the London School of Hygiene and Tropical Medicine.

**ORGANISATIONAL CAPACITY**

# UNIVERSITY OF DAKAR - SENEGAL

L'Université Cheikh Anta Diop (UCAD), located a few hundred yards from the Atlantic Ocean, is the oldest university in West Africa. Created during the French colonial era as the School of Higher Studies (L'Ecole de Haute Etudes), UCAD served all of French West Africa and contributed to the training of the first intellectuals, medical doctors, and academics in the region. The institution was later renamed the Université de Dakar and then L'Université Cheikh Anta Diop after one of Africa's most prolific and respected historians whose works (such as Civilization or Barbarism) note the parallels and brings into question the various cultural influences between "Black African" civilization and Egyptian civilization. Today, UCAD is Senegal’s largest university and is reputed to be the finest in francophone Africa. Some 43000 students from all of West Africa attend classes on this lively and friendly campus; it is not uncommon to see students from Sierra Leone in lively conversation with others from Mauritania and America. This sIPTc implementation project would mean strengthening of research activities on malaria, which are done with international standards. It would also provide a unique opportunity of training a pool of medical students of on field research.

# FRENCH RESEARCH FOR DEVELOPMENT INSTITUTE - SENEGAL

The IRD is a French public science and technology research institute under the joint authority of the French ministries in charge of research and overseas development. The IRD has three main missions: research, consultancy and training. It conducts scientific programs contributing to the sustainable development of the countries of the South, with an emphasis on the relationship between man and the environment.

# LONDON SCHOOL OF HYGIENE AND TROPICAL MEDICINE – UNITED KINGDOM

The London School of Hygiene and Tropical Medicine (LSHTM) was founded in 1899. Its charter received royal approval in 1924. LSHTM celebrated its centenary year in 1999. LSHTM’s mission is to contribute to the improvement of health worldwide through the pursuit of excellence in research, postgraduate teaching and advanced training in national and international public health and tropical medicine, and through informing policy and practice in these areas.

**BUDGET JUSTIFICATION**

1. Institutional fees

A rate of 10% of the requested budget, excluding equipment fees, has been used for overheads.

2. Personnel

For this implementation study, human resources will be decisive. An experienced, professional and well-motivated team of field-physicians, nurses and field workers is needed. At times, about sixty (60) local staff will be involved simultaneously in the field. All payments have been worked out according to the Senegalese salary scale.

Assistance of an IT manager is fundamental for design of the data management system, supervision of data entry and safekeeping of the data.

3. Equipment

For this study, good logistical support will be essential, as during the rainy season, the environment is unfavorable with poor quality of roads, power failures etc... Reliable 4X4 cars, motorbikes and generators are required for both implementation and evaluation teams. It is also planned to provide all the 48 health posts with basic medical equipment that will help to improve the health care delivered to all-those who attend. The offices of the study in Dakar will be equipped with basics tools such as computers and accessories.

4. Travel

For any member of the project directorial or any recruited consultant, the project will pay the cost of all journeys related to coordination, supervision, training or presentation of results.

5. Coordination and training

Coordinating such a trial will need a staff that is fully committed to the project. This will be done by the PIs. The project coordinator (full time PI) is a clinical epidemiologist who has overseen a number of Gates Malaria Partnership projects, in the capacity of project leader in Senegal. All these projects were very well managed and successfully completed. In addition, he has completed a Master of Sciences at the LSHTM in 2001. He successfully completed in September 2005 his PhD and is now based at the University of Dakar (Department of Medical Parasitology and Mycology) as a visiting lecturer.

The project will represent a unique opportunity for several young Senegalese scientists to gain experience in field research and implementation of large-scale programme to control malaria. Sadly, this area of research is presently neglected in many developing countries. This must be a point of great concern.

6. Mortality survey in year 1

The survey will be conducted immediately after the end of the 2006 malaria season, preliminary mapping from October 2006 and house-to-house interviews from December 2006 to March 2007, with data processing and statistical analysis continuing until June 2007. We will require 10 teams of two field workers and 3 supervisors, with additional costs for mapping, printing questionnaires, data entry, computers and software, logistic support, and consultancy visits from a survey specialist. Alternative funding has been sought for this survey and we therefore do not request funds for this in the present budget,

# APPENDIX 1: Record form for inclusion & follow-up

______________________

District number |___|___| Village name & number |___|___|___|

Household owner Hamlet name:

# Mother name Mother’s ID Number: |___|___|___|___|___|___|

Mother age |___|___| Mother occupation

##### *Mother educational background* |___| (0=no, 1=primary, 2=secondary or more, 9=info no available)

# Child name: ID |___|___|___|___|___|___| - |___| Age |___|___| Sex |___|

|  | June/July  Ethics | August  Screening | September  1st sIPTc dose | October  2nd sIPTc dose | November  3rd sIPTc dose | December  Evaluation |
| --- | --- | --- | --- | --- | --- | --- |
| Date of visit |  |  |  |  |  |  |
| Auricular temperature | NA[[1]](#footnote-2)* |  |  |  |  |  |
| Drugs administered at home/health facility | NA | NA |  |  |  |  |
| Haemoglobin (g/dL) | NA | NA | NA | NA | NA |  |
| MPs/Per 200WBC | NA | NA | NA | NA | NA |  |
| Filter paper sample | NA | NA | NA | NA | NA |  |
| Weight (Kg) | NA |  | NA | NA |  | NA |
| Height (cm) | NA |  | NA | NA |  | NA |
| Mid arm circumference | NA |  | NA | NA |  | NA |
| Drugs retention (Y/N) | NA | NA | NA |  |  |  |
| Action taken if vomited | NA | NA |  |  |  | NA |

COMMENTS**:……………………………………………………………………………….…………………………………………………………………………………………………………………………………………………………………………………………………………………………………………………………………………………………………………………………………………………………………………………………………………………………………………………………………………………………………………………………………………………………………………...**

APPENDIX 3: Malaria episodes: clinical & laboratory data at days 0, 3, 7 & 14

#### _______________________________

Child name: ID |___|___|___|___|___|___| **-** |___| Age |___|___| Sex |___|

# Mother name:

District number |___|___| Village name & number |___|___|___|

Household owner: Hamlet name:

| Day of Protocol | D0 | D3 | D7 | D14 |
| --- | --- | --- | --- | --- |
| Date |  |  |  |  |
| Time |  |  |  |  |
| Temperature |  |  |  |  |
| Pulse |  |  |  |  |
| Respiratory Rate |  |  |  |  |
| Spleen Size |  |  |  |  |
| Parasitemia |  |  |  |  |
| Gametocytemia |  |  |  |  |
| Hemoglobin |  |  |  |  |

| Day of Protocol | D0 | D3 | D7 | D14 |
| --- | --- | --- | --- | --- |
| Fever/chills (Y/N) |  |  |  |  |
| Headache (Y/N) |  |  |  |  |
| Vomiting (Y/N) |  |  |  |  |
| Lethargy/abnormal consciousness (Y/N) |  |  |  |  |
| Convulsions (Y/N) |  |  |  |  |
| Respiratory distress (Y/N) |  |  |  |  |
| Able to eat or drink (Y/N) |  |  |  |  |
| Other (Y/N)  -  - |  |  |  |  |

APPENDIX 4: Serious adverse event report form

### ___________________

Child name: ID |___|___|___|___|___|___| **-** |___| Age |___|___| Sex |___|

# Mother name:

District number |___|___| Village name & number |___|___|___|

Household owner: Hamlet name:

| Date of serious adverse event: | | / / | |
| --- | --- | --- | --- |
| Location of sae (e.g., at home, health post or elsewhere): | |  | |
| Was this an unexpected adverse event? | | yes [ ] no [ ] | |
| Brief description of subject (do not include identifiers.) | | sex: m/f age:  diagnosis: | |
| Brief description of the nature of the serious adverse event: | | | |
| Category (outcome) of the serious adverse event:  [ ] death  [ ] life threatening  [ ] hospitalization  [ ] persistent or significant disability/incapacity  [ ] congenital anomalies or birth defects  [ ] other conditions which in the judgment of the investigators represent significant hazards | Relationship of serious adverse event to research:  [ ] 1 = unrelated (clearly not related to the research)  [ ] 2 = unlikely (doubtfully related to the research)  [ ] 3 = possible (may be related to the research)  [ ] 4 = probable (likely related to the research)  [ ] 5 = definite (clearly related to the research) | | |
| Have similar adverse events occurred on this protocol? | yes [ ] no [ ]  if “yes”, how many?  please describe: | | |
| What steps do you plan to take as a result of the adverse event reported above? provide documentation to the irb for review and approval of any of the steps checked below. | [ ] no action required  [ ] amend consent document  [ ] amend protocol  [ ] inform current subjects  [ ] terminate or suspend protocol  [ ] other, describe: | | |
| Investigator’s name & signature: | | | Date: / / |

# APPENDIX 5: Documentation of termination of participation in the study

______________________

Child name: ID |___|___|___|___|___|___| **-** |___| Age |___|___| Sex |___|

# Mother name:

District number |___|___| Village name & number |___|___|___|

Household owner: Hamlet name:

Participation of the volunteer in the study has been terminated because (check only one box):

 The parents’ volunteer want to stop participating in the study

Reason

________________________________________________________________________

________________________________________________________________________

________________________________________________________________________

 The study monitor believes it is not in the best interest of the child to continue in the study.

Reason

________________________________________________________________________

________________________________________________________________________

________________________________________________________________________

The parents have been informed of withdrawal and the justification for withdrawal

Signature of the Investigator _________________________________ Date ______

APPENDIX 6: summarized budget (in us $)

|  | **2007 & 2008** | **2009** | **2010** | **Total** |
| --- | --- | --- | --- | --- |
| Total Personnel | 496 215,00 | 612 735,00 | 729 255,00 | 1 838 206,00 |
|  |  |  |  |  |
| **Total Travel** | 22 000,00 | 22 000,00 | 22 000,00 | 66 000,00 |
|  |  |  |  |  |
| **Total Equipment** | 321 330,00 | 207 300,00 | 254 800,00 | 783 430,00 |
|  |  |  |  |  |
| **Medical and Laboratory** | 24 000,00 | 76 000,00 | 120 000,00 | 216 000,00 |
|  |  |  |  |  |
| **Other Supplies** | 10 500,00 | 10 500,00 | 10 500,00 | 31 500,00 |
|  |  |  |  |  |
| **Total Consultants** | 21 000,00 | 21 000,00 | 21 000,00 | 63 000,00 |
|  |  |  |  |  |
| Subtotal of Direct Costs | **895 045,00** | **945 535,00** | **1 157 555,00** | **2 998 135,00** |
|  |  |  |  |  |
| Overheads | 102 541,00 | 119 921,00 | 151 333,00 | 373 795,00 |

**Statistical Analysis Plan**

**Dec 2013**

Outcomes:

All-cause mortality in children aged 3-59 months and 60-119 months (primary outcome)

Cause of deaths in 13 health post areas where verbal autopsies will be performed

Incidence of RDT-confirmed malaria

Incidence of malaria (confirmed and unconfirmed)

Incidence of severe malaria (admission to hospital with primary diagnosis of malaria)

IPTc Coverage: proportion who received 1,2 and 3 courses of IPTc, and the proportion who received no IPTc, each year of the study

ITN Coverage

Prevalence of parasitaemia at the end of each transmission season

Prevalence of gametocyte carriage

Prevalence of anaemia (moderate: Hb<11g/dL and severe: Hb<6g/dL)

Mean haemoglobin concentration

Prevalence of drug resistance markers

Serology: prevalence of antibodies to CSP, MSP1 and AMA1

Costs of IPTc delivery: financial and economic costs to the provider

Incidence of serious adverse drug reactions

Baseline characteristics:

Characteristics of the 6 implementation zones will be tabulated, including DSS estimates of population size of children and including all age groups, bednet use recorded in each DSS round in children under 10 years and in older age groups, the mean distance to the nearest health facility, socio-economic status, religion and ethnicity.

Mortality rates:

The mortality rate ratio for the effect of IPTc will be estimated using Poisson regression with a gamma-distributed random effect for the cluster. An indicator variable for the intervention effect in each age group (3-59 months and 60-119 months) will be defined, set to 1 for each time period, age group and cluster when IPTc was implemented and set to 0 otherwise. A test of interaction will be done and combined estimate of intervention effect estimated if there is no evidence of an interaction. Age group (<3 months, 3-59 months, 60-119 months), and calendar year (2008,2009,2010) and zone will be included as covariates in the model. All deaths recorded in the DSS system will be included with person time obtained from the DSS. The DSS here refers to the DSS system set up for this project, and the Niakhar DSS. Person time includes all persons resident in the DSS area, from study start, date of birth or immigration, and censored when they left permanently or died. Temporary absence will not be accounted for as these dates are judged to be not sufficiently accurate and complete in the project DSS. Data updated to DSS round 4 will be included in the primary analysis.

Time periods:

Primary analysis of rates will be for the period from September 15 to December 15 each year. Secondary analysis will be done using data for the whole year.

Malaria incidence:

A similar model will be fitted to estimate the malaria incidence rate ratio. This will be done firstly for malaria cases that were confirmed by RDT or slide (i.e. cases treated for malaria at a health facility with a positive diagnostic test result), and secondly including all cases treated for malaria with or without confirmation. Two indicator variables for the intervention effect will be defined, the first one for direct effects* is set to 1 for each time period, age group and cluster when IPTc was implemented and 0 otherwise, the second for indirect effects is set to 1 in IPTc clusters for all age groups too old to receive the intervention, and 0 otherwise. For the direct effects, a test of interaction will be done and combined estimate of intervention effect estimated if there is no evidence of an interaction. Age group (0-59 months, 60-119 months, 10-20 years, 20-30 years, 30-40 years, 40-50 years, 50-60 years and 60+), and calendar year (2008,2009,2010) will be covariates in the model. The first age group is 0-59 months rather than 3-59 months because clinic records do not reliably note if the child was under 3 months of age. Malaria cases will be linked to the cluster (health post) based on the village of residence recorded in the register, not the health post where the case was treated. All cases at health huts, health posts, mission clinics, health centres and regional hospitals will be included. A list of the names of all villages and hamlets was prepared, 1247 in total, these were assigned a numeric code, this list was used when project staff visited health facilities to collect malaria data, to check if the village was within the project area, and assign a numeric code to the village of residence, or a code to indicate the village was outside the area.

*Note the model estimates indirect effects in the older age groups, while the effect in the intervention age groups represents total direct plus indirect effects. The direct effect of IPTc would be D=(T-I)/(1-I) where I is the indirect effect, if any, in older age groups, and T the total effect, observed in children.

The same DSS data as for mortality analysis were used for analysis of malaria incidence. For the rebound analysis, data updated to round 5 were included in the rebound analysis. Round 5 was incomplete (healthposts not visited in round 5: 39 DAROU SALAM, 41 GRAND MBOUR, 44 MBALLING, 45 MEDINE, 46 NGAPAROU, 47 NGUEKHOKH I, 48 NGUEKHOKH II, 49 POINTE SARENE,

50 SALY, 51 SANTESSOU, 54 VAREDO) for this reason population denominators for the rebound analysis were obtained by projection from the 2008-2010 data assuming a uniform annual growth rate of 3.6%.

Incidence the year after intervention will be compared between PSP and control areas in age groups that reflect the number of previous years of IPTc received, using a random effects poisson regression with adjustment for age effects.

Estimates of the coefficient of variation between clusters will be estimated for the main incidence rate endpoints (mortality and malaria), as √α where α is the variance of the exponentiated random effect reported by Stata in the xtpoisson output, from a model without covariates and from a model with covariates.

Analysis of cross-sectional surveys:

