## General Objective

- To assess the effectiveness of seasonal IPT when delivered through health services, with community participation.
- To evaluate the impact of sIPT in children on all-causes mortality.

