Here “X” represents a group of 8 zones (16,000 children 3-59 months) receiving intervention, “0” represents a group of 8 zones that are kept under malaria and mortality surveillance but which have not yet received the intervention. For groups “0”, intervention is delivered the following year. Thus, intervention is gradually phased in, in the first year we will intervene in 8 zones, in the second year in 24 zones, and in the third year in 40 zones, and in the 4th year in all 48 zones. This design enables a statistically efficient and unbiased comparison of mortality rates with and without the intervention. In year 4, implementation will be taken over by the Ministry of Health and the community. Rebound effects in children over 5 yrs will be assessed through a case control study.

Prior to the implementation study, a four-months survey will be conducted to estimate mortality rates under children five years in the three districts of the study area. This cross sectional study will also determine socio economic predictors of areas with a high mortality.

2.1. Pilot cluster sample survey to determine under five mortality rates in the 3 districts of the study area

The sample size and design of the study rely on good estimates of childhood mortality rates. Excellent estimates are available from the Niakhar area from demographic surveillance, but we do not know the situation in the other parts of the study area. In addition, for efficient evaluation of the impact of sIPTc on mortality it is important that we stratify health zones into strata of similar mortality rate before randomization. However, correlates of higher mortality on which stratification could be based are not well known, this survey will provide an opportunity to determine these correlates. Lastly, the survey will allow us to estimate the coefficient of variation of mortality rates between zones, an important quantity in the sample size calculation for the randomized implementation study.

We will therefore conduct a survey to estimate mortality rates among children under 5 years in the three districts of the study area, and determine socioeconomic predictors of areas of high mortality.

The area will be divided into four strata for survey purposes, these will be:

1. The area of the Niakhar DSS.
2. The remaining part of Fatick district not covered by the DSS.
3. Bambey district (excluding DSS).
4. Mbour district.

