***- Administration of sIPTc***

In the first year of the trial, registers of eligible children will be established in Stratum A comprising 16 zones. sIPTc will be administered in only 8 of these zones, selected at random. Throughout the study area antimalarial treatment according to the national guidelines will be available in the health post (Figure 3).

In the second year of the trial, the intervention will be extended to the remaining 8 zones of Stratum A and also it will be introduced in 8 new zones in Stratum B.

In the third year of the trial, intervention will be extended to the remaining 8 zones of Stratum B and to 8 new zones in Stratum C.

In each stratum, implementation will be taken over by the Ministry of Health and the trial communities in the second year of implementation.

**Figure 3**: A simplified model of the study design and diverse types of comparison.

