**- Drug sensitivity of *P. falciparum***

In order to assess the impact of the intervention on the sensitivity of *P. falciparum* to antimalarials, *in vivo* tests and molecular markers studies will be undertaken.

For sulfadoxine-pyrimethamine resistance investigations, molecular markers studies (DHFR and DHPS) will be conducted each year at the community levels, before and after the intervention. In addition to the thick smear, a drop of blood will be taken on a filter paper in a random sample of children at the end of the malaria season transmission., Markers of resistance to pyrimethamine and sulfonamides will be detected using a PCR assay as previously described (Pearce et al. 2003)

For evaluation of sIPTc for all these endpoints, data from Stratum A in year 1, Stratum B in year 2 and Stratum C in year 3 will be used in a stratified analysis comparing zones with and without sIPTc (Figure 4).

3. Safety studies

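### A single on/off IPTc indicator gives no rate ratio for later seasons, and if the effect fades the one mortality ratio leans towards the first-season effect

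*Combined protocol and SAP*

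**What the plan says.** **Objective.** The protocol summary sets out "To assess the effectiveness of seasonal IPT when delivered through health services, with community participation". The specific objectives add sustainability of delivery and rapid change in drug sensitivity.

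**Primary model (SAP, Mortality rates).** The rate ratio is "estimated using Poisson regression with a gamma-distributed random effect for the cluster". The IPTc indicator is defined for each of the two eligible age groups and is "set to 1 for each time period, age group and cluster when IPTc was implemented and set to 0 otherwise". The one interaction test described is between those age groups. Covariates: "Age group (<3 months, 3-59 months, 60-119 months), and calendar year (2008,2009,2010) and zone will be included as covariates in the model". Risk period: "Primary analysis of rates will be for the period from September 15 to December 15 each year". The malaria incidence model codes IPTc the same way, but its covariate list gives age group and calendar year and not zone.

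**Hand-over.** Three protocol statements differ:
- Phased introduction (section 6): "In each stratum, implementation will be taken over by the Ministry of Health and the trial communities in the second year of implementation".
- Design, sample size and power calculations (section 2): "In year 4, implementation will be taken over by the Ministry of Health and the community".
- Drug administration (section 3): the national malaria programme is responsible for delivery, with no distinction of phase.

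**Protocol contrast for the impact endpoints.** At the end of the drug-sensitivity text, "data from Stratum A in year 1, Stratum B in year 2 and Stratum C in year 3 will be used in a stratified analysis". Each of those strata is then in its first season.

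**Related SAP items.** IPTc coverage is reported for each study year. Resistance markers are compared between intervention and control areas year by year. The rebound analysis already groups children by number of previous years of IPTc.

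**The concern.** In a phased roll-out with zone and year terms, a zone already on IPTc also helps set the comparison for zones that start later. One indicator for all treated seasons is then harmless only if the effect is constant. If protection or coverage falls after the first season, the single ratio is a weighted combination that favours first seasons, and nothing else in the plan would show the fall in mortality or malaria terms.

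At stake is the reading of the main result. A reader would take the ratio as the benefit of the programme as it settles into routine use, when it mainly describes the first season. The marker comparison has a related gap: under the phasing, intervention areas in 2009 and 2010 mix different lengths of drug pressure.

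**Working it through.** **Plan's own figure.** The protocol gives 22 clusters per arm for 90% power at 20 deaths per 1000 child-years, a 27% reduction, 2000 children per cluster and k = 0.25. The usual formula for rates in cluster-randomised trials, with two-sided 5% assumed, gives

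c = 1 + (1.96 + 1.28)² × [(0.02 + 0.0146)/2000 + 0.25² × (0.02² + 0.0146²)] / 0.0054² = 21.04, which rounds up to 22.

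The figure reproduces, so 0.73 is used below as the first-season ratio.

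**Roll-out.** The SAP states that 45 of 54 posts were on IPTc in 2010, and that zones 1, 2 and 6 held 27 posts, an average of 9 per zone. The protocol phases in 8, 24 and 40 of 48 clusters. Assumed here: 9, 27 and 45 posts, that is one zone starting in 2008, two in 2009, two in 2010 and one never.
- 3-59 months: 9 + 27 + 45 = 81 treated post-years. Of these, 9 + 18 + 18 = 45 (56%) are first seasons and 27 + 9 = 36 (44%) are second or third.
- 60-119 months: the SAP survey section shows this group was not eligible in 2008. Counting from the group's own start, 9 + 18 + 18 = 45 are first seasons and 27 are later.

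**Post-year averages, 3-59 months (log scale).**
- 0.73 then 0.87: exp[(45 ln 0.73 + 36 ln 0.87)/81] = 0.79.
- 0.73 then 1.00: exp[(45 ln 0.73)/81] = 0.84.

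**3-59 months alone, zone and year terms, one indicator.** With equal weights, the estimated log ratio puts weight 1.25 on first seasons, 0 on second and -0.25 on third. A Poisson model fitted to expected counts gives:
- 0.73 then 0.87: 0.71.
- 0.73 then 1.00: 0.69.
- 0.87 then 0.73 (effect grows): 0.90.

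Each lies outside the two true values.

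**Model as the SAP writes it.** This adds children under 3 months, who never receive IPTc, and those aged 60-119 months, all sharing the zone and year terms. The documents give no mortality rates for these ages. Assumed: 50-200 and 3-6 deaths per 1000 per year, with about 110 and 1900 children per post. Expected-count fits give:

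| True ratio, first then later | Single estimate | Post-year average (3-59 months) |
|---|---|---|
| 0.73 then 0.87 | 0.74-0.76 | 0.79 |
| 0.73 then 1.00 | 0.74-0.79 | 0.84 |

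The estimate lies between the phases, closer to the first season than the average is.

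**With the gamma random effect.** Three hundred simulated fits per scenario, 54 clusters, k = 0.25, three age groups and zone included, gave 0.756 for a true 0.73 then 0.85. The average there is exp[(45 ln 0.73 + 36 ln 0.85)/81] = 0.78. With a constant 0.73 the fit returned 0.734, so the lean appears only if the effect changes.

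**Two indicators (first season; second or later).** The expected-count fits return both true values. The SE of the later-season log ratio is about 0.16 for 3-59 months alone and 0.09-0.12 with three age groups. These take 2000 × 0.02 × 0.25 = 10 deaths per post per risk period at ages 3-59 months and ignore between-cluster variation. Around a true 0.87, SE 0.09 gives a 95% interval of 0.87 × exp(±1.96 × 0.09) = 0.73 to 1.04. SE 0.16 gives 0.64 to 1.19.

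**The case against.** **Inferring that the single ratio must look better than either phase.** A reader might infer this from the 3-59 month results of 0.71 and 0.69. The SAP model does not support it. The under-3-month group supplies untreated information within each zone and year, and over the assumed rates the estimate stays between the phases. What stands is the lean.

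**Inferring project-led first seasons followed by Ministry-run seasons.** Only the phased-introduction section supports a hand-over in the second season. The design section puts it in year 4, which is outside 2008-2010 if year 1 is 2008. The drug-administration section makes the national programme responsible from the start. So the documents do not show that effectiveness under routine delivery goes unestimated, since delivery may be through the health services throughout. The supportable split is first against later season.

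**Malaria incidence.** The zone-and-year argument does not carry over, because that model lists no zone covariate and adds untreated older age groups. An illustrative fit without zone, random effect or indirect term gave 0.78 and 0.82, near the averages of 0.79 and 0.84. The missing later-season ratio still applies, but the lean is not shown there.

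**Partly covered elsewhere.** Coverage is reported yearly, and the 2008 marker comparison contains first seasons only. Neither gives a later-season effect on mortality.

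**The fade is hypothetical.** No document gives a later-season effect. This is accepted: the point is that the plan could not show a fade, not that one is expected.

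**Conclusion.** The concern holds in a limited form. The mortality and malaria models assume equal effects in first and later seasons, and no rate ratio is planned for later seasons, which under the assumed phasing are 44% of treated post-years at ages 3-59 months. If the effect fades, the mortality ratio leans towards the first season. A complete loss of benefit after season 1 could still be reported as a 21-26% reduction (1 - 0.79 to 1 - 0.74), against 16% averaged over post-years (1 - 0.84) and the 27% used for the sample size.

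These sizes rest on the assumed 9/27/45 phasing, the assumed rates outside 3-59 months, and illustrative fades. With a constant effect the planned analysis is sound, so the primary model need not be replaced.

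**What to change.** - **Mortality.** Keep the primary model. Prespecify a secondary model with two indicators, first season and second or later season of implementation, defined separately for 3-59 and 60-119 months. State how the older group in the first zone is classed in 2009, when the zone is in its second season but that age group is in its first.
- **Reporting.** Give both rate ratios with intervals, plus an average weighted by actual post-years in each age group. A fixed 45:36 weight would not suit 60-119 months (45:27 under the same phasing). Making the average the primary result would change the estimand, so it belongs with the secondary results.
- **Malaria incidence.** Fit the same split descriptively.
- **Coverage and markers.** Tabulate IPTc coverage and resistance-marker prevalence by number of seasons of implementation (0, 1, 2, 3).
- **Hand-over.** Reconcile the design, drug-administration and phased-introduction sections on who delivers and when, before any phase is labelled by provider.

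Cost: SAP wording, one secondary model and some tables, with no new data. The later-season estimate will be imprecise, and between-cluster variation will widen its interval further, so an inconclusive later-season ratio should not be read as loss of effect.
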